### Participants

The study will include outpatient INPC primary care practices operating in urban and rural settings that are part of the INPC, representing multiple health systems and clinics. Clinics that do not use the DOCS4DOCS® software will be excluded.

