We hypothesize clinics that implement the intervention will effectively incorporate the pre-populated reporting form into their workflow, providers will report high satisfaction with the intervention, and that, compared to clinics in which the intervention is not implemented, barriers to reporting will be reduced, timeliness of reporting and completeness of report data fields will improve, and need for providers to provide supplemental or corrected data to public health will be reduced. The implementation of the intervention will be evaluated using mixed methods. The study protocol described will evaluate the implementation of the pre-populated form intervention in the context of an operational HIE.

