### Setting

The intervention will be implemented within one of the largest and oldest HIE infrastructures in the U.S., the Indiana Network for Patient Care (INPC). The INPC is anchored by the Regenstrief Medical Record System which collects data from a variety of sources, including hospitals, clinics, pharmacies, and laboratories
[19]. Lab results are routinely delivered to ordering physicians using the Regenstrief DOCS4DOCS® software and analyzed as ELR transactions by the Notifiable Condition Detector (NCD) which identifies mandated reportable diseases and notifies local and state public health departments of these laboratory results
[20].

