### Intervention

Two technical interventions will be deployed over a staggered schedule at participating clinics: 1) “standard” pre-populated forms and 2) “enhanced” pre-populated forms. The “standard” forms intervention will use EHR (patient demographics and clinic information) and ELR (notifiable disease test results) data available in the HIE to pre-populate and deliver an electronic version of the official state notifiable disease reporting form to the provider. Providers will be able to review the pre-populated form, add any additional information, and fax completed forms to their local health department. The “enhanced” forms intervention will pre-populate an alternative reporting form with an expanded set of data available in the HIE. For example, the “enhanced” form will not only include test results data for a case of hepatitis B but also corollary results on the patient’s liver enzymes; this is information the health department typically requests from the provider in a follow-up phone call when investigating the reported case of hepatitis. Providers will still be able to review the pre-populated “enhanced” form, add any additional information, and fax completed forms to their local health department. Since deployment is staggered, at any point in time the non-intervention sites can act as natural controls for the intervention sites without the selection bias that is generally present in non-randomized experiments. Therefore, the study protocol is theoretically equivalent in its ability to generate causal evidence to a traditional randomized controlled experiment.

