### Limitations and biases

There are several limitations to our proposed work. First, some clinical sites may be more open to recruitment and enrollment in the study and thus introduce a bias in our sample. For example, some sites may serve patient populations that are more likely to require notifiable disease reporting (for example, a women’s clinic with a high Chlamydia reporting history) and thus be more incentivized to participate. It is possible given use of an interrupted time-series design, that confounding may occur due to covariates that may change over time. The INPC is a growing HIE so it is possible that policy, governance, legal mandates or information technology changes could occur during the course of this study that may impact data collection or introduce additional confounding issues. This HIE includes an academic affiliation and medical training program so providers may rotate through training sites at different stages of the intervention which may introduce confounding. Introduction and adoption of the intervention may be more rapid in some settings (small ambulatory clinic) than others (large hospital) as the workplace may accommodate or adjust to the intervention more easily or require administrative protocols to support the intervention. It is also possible that the staggered implementation of the intervention may complicate quality control of data collection. Also, given data collection covers only one baseline year and a maximum of two years post-intervention, depending on site, this short time frame may limit ability for analysis to account for seasonal trends in reporting. Our findings may also be limited by the context in which this study is conducted. The INPC is one of the most advanced HIEs in the country; therefore, our results may have limited generalizability. However, we believe our emphasis on context and by clearly documenting the characteristics of the sites in which the intervention, our findings could inform implementation other HIE settings. Given current mandates to build systems and infrastructures for ELR and HIE in communities where it is absent, expand efforts in communities where ELR is already occurring, and requirement for eligible hospitals to routinely transmit reportable laboratory results to a public health agency, our findings may provide insights and inform roadmaps for more nascent HIEs to move forward towards better notifiable disease surveillance.

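### The claim that untreated control clinics exist at any point in time can hold only until the last clinic goes live, so an unexposed concurrent control for the enhanced form is not assured

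*Protocol article*

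**What the plan says.** All places are in the protocol article.

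- **Participants:** the study takes INPC outpatient primary care practices, and "Clinics that do not use the DOCS4DOCS® software will be excluded". **Setting** explains the role of that software: "Lab results are routinely delivered to ordering physicians using the Regenstrief DOCS4DOCS® software".
- **Intervention:** "Two technical interventions will be deployed over a staggered schedule at participating clinics". The control concept follows: "Since deployment is staggered, at any point in time the non-intervention sites can act as natural controls for the intervention sites". From this the section concludes that the protocol is "theoretically equivalent in its ability to generate causal evidence to a traditional randomized controlled experiment".
- **Background:** the hypothesis on barriers, timeliness, completeness and supplemental data is stated "compared to clinics in which the intervention is not implemented".
- **Data collection:** there are three phases (baseline, after the standard form, after the enhanced form). Table 1 plans the comparison of the two forms as pre-post.
- **Data analysis (quantitative):** longitudinal effects are assessed by interrupted time series, with reference to multiple-baseline designs.
- **Limitations and biases:** there is one baseline year and at most two years after the intervention, depending on site. Policy, governance, legal or technology changes may occur during the study.

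The article does not give the number of clinics, the order or spacing of go-lives, or when the enhanced form starts relative to the last standard-form go-live.

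**The concern.** The controls in this design come from the staggering: clinics not yet live stand beside clinics already live. Both forms go to the participating clinics, and no participating clinic is described as remaining without them. Such a pool shrinks with each go-live and is empty after the last one, so the claim about any point in time cannot hold for the whole follow-up.

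The causal claim rests on that sentence, and the Background hypothesis needs clinics without the intervention as its comparator. Once all clinics are live, no such clinic remains among the participants. A legal or technology change in those months then coincides with form use everywhere and cannot be separated from the form effect there. The enhanced form is most affected because it comes last.

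**Working it through.** The article states no figure to reproduce, so the check is a count of calendar time under assumed schedules.

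**Inputs from the article:** both forms go to participating clinics, staggered; the standard form precedes the enhanced form; follow-up is at most two years after the intervention.

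**Assumptions:** all participating clinics go live; 7 clinics at equal steps; rollout span R from first to last standard-form go-live of 3 to 18 months; each clinic uses the standard form for S = 6, 9 or 12 months before the enhanced form; the window closes 24 months after the first go-live.

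**Formulas**, in months from the first go-live:

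1. An unexposed participating clinic exists from month 0 to month R, that is for R of 24 months.
2. The first enhanced go-live is at month S, so the enhanced phase lasts 24 − S months.
3. Enhanced-phase months with an unexposed clinic = max(0, R − S).
4. Enhanced-phase months with a clinic still unexposed or on the standard form = min(R, 24 − S), because the last clinic leaves the standard form at month R + S.

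**Results for formula 1:** from 3 of 24 months (12.5%) at R = 3 to 18 of 24 (75%) at R = 18, and none after that.

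**Results for formulas 3 and 4** (unexposed only / unexposed or on the standard form, in months):

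| | R=3 | R=6 | R=9 | R=12 | R=15 | R=18 |
|---|---|---|---|---|---|---|
| S=6 (enhanced phase 18) | 0 / 3 | 0 / 6 | 3 / 9 | 6 / 12 | 9 / 15 | 12 / 18 |
| S=9 (enhanced phase 15) | 0 / 3 | 0 / 6 | 0 / 9 | 3 / 12 | 6 / 15 | 9 / 15 |
| S=12 (enhanced phase 12) | 0 / 3 | 0 / 6 | 0 / 9 | 0 / 12 | 3 / 12 | 6 / 12 |

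The overlap with an unexposed clinic is zero whenever R is at most S. Otherwise it covers only part of the enhanced phase.

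**The same in clinic-months.** Take go-lives at months 0, 2, ..., 12 and let every clinic complete 12 months on each form, which is 7 × 12 = 84 clinic-months per form. This needs 36 months in all, so here the 24-month window is not imposed.

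- Standard form, with an unexposed clinic running: 12+10+8+6+4+2+0 = 42 of 84 (50%).
- Enhanced form, with an unexposed clinic running: 0 of 84, since no clinic starts it before month 12.
- Enhanced form, with a clinic still on the standard form: the last clinic switches at month 24, so again 12+10+8+6+4+2+0 = 42 of 84 (50%).

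**What the assessment times suggest.** Quantitative data are collected up to 12 months after implementation of both forms, and interviews are held 12 months after each form. Read as 12 months per form, S is about 12. If there is also a common closing date at month 24, a clinic reaches its 12-month standard-form assessment only if it goes live by month 12. Then R is at most 12 and the overlap with an unexposed clinic is 0. The common closing date is an assumption, so this indicates the likely case and does not prove it.

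**The case against.** A staggered or multiple-baseline design does not need a never-exposed group. Each clinic's own prior trend, together with not-yet-exposed clinics during rollout, supplies the comparison. The Background hypothesis can be read as referring to not-yet-exposed clinics, and the limitations section already discloses confounding over time. All of this stands. It defends the design, but not the statement that controls exist at any point in time or the equivalence to a randomised experiment drawn from it.

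A reader might go further and infer that the DOCS4DOCS exclusion causes the problem, by removing the only never-exposed comparators. The article does not support that:

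- The exclusion is an eligibility condition for a network whose laboratory results reach physicians through this software. Controls run out because the participating clinics all go live, which would happen under any eligibility rule.
- Clinics outside the software are not shown to be the only candidates. The limitations section says "some clinical sites may be more open to recruitment and enrollment in the study and thus introduce a bias in our sample", so DOCS4DOCS clinics that do not enrol may exist and would also be unexposed. Table 1 and its key do not limit the report-form census to participants.

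A reader might also infer that the enhanced phase can have no concurrent control. That depends on a schedule the article does not give. It is wrong for spans R longer than S, and it overlooks clinics still on the standard form, which are the comparator Table 1 has in mind for the enhanced form.

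**Conclusion.** The point holds as a fault in the Intervention section. If all participating clinics go live, as that section indicates, unexposed controls are confined to the rollout window. For the enhanced form an unexposed concurrent control is absent when the rollout takes no longer than the standard-form period, and covers only part of the phase otherwise (0 to 12 months over the schedules examined). A concurrent standard-form clinic exists for some of the enhanced phase in every schedule examined, but that comparison answers a different question from the Background hypothesis.

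After the last go-live, that hypothesis cannot be tested between clinics within the study. Attribution then rests on each clinic's own earlier trend, which an outside change would disturb.

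The sizes depend on assumed values of R and S and on a 24-month window. The loss of unexposed participants after the last go-live depends only on all of them going live. The DOCS4DOCS rule itself is not an error. Whether the equivalence claim is justified inside the rollout window is a separate question, not examined here.

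**What to change.** Leave the eligibility rule in Participants as it is. In Intervention:

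1. State that not-yet-exposed clinics serve as controls only until the last go-live.
2. Limit between-clinic causal claims, including the Background hypothesis, to that window.
3. Drop the claim of equivalence to a randomised experiment for the months after it.
4. State that the enhanced form is compared with clinics concurrently on the standard form and with each clinic's own earlier series.

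These are wording changes, with no new data and no change to the rollout.

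Optionally, where the report-form census already covers them, add never-exposed INPC practices as a supportive comparison of changes from their own baseline: non-enrolled DOCS4DOCS clinics first, other practices second. The cost is coding their report forms. The downside is that such clinics may differ systematically from participants, and those outside DOCS4DOCS may not share the same technology changes. This series should therefore not carry the main conclusion.

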### Intervention

Two technical interventions will be deployed over a staggered schedule at participating clinics: 1) “standard” pre-populated forms and 2) “enhanced” pre-populated forms. The “standard” forms intervention will use EHR (patient demographics and clinic information) and ELR (notifiable disease test results) data available in the HIE to pre-populate and deliver an electronic version of the official state notifiable disease reporting form to the provider. Providers will be able to review the pre-populated form, add any additional information, and fax completed forms to their local health department. The “enhanced” forms intervention will pre-populate an alternative reporting form with an expanded set of data available in the HIE. For example, the “enhanced” form will not only include test results data for a case of hepatitis B but also corollary results on the patient’s liver enzymes; this is information the health department typically requests from the provider in a follow-up phone call when investigating the reported case of hepatitis. Providers will still be able to review the pre-populated “enhanced” form, add any additional information, and fax completed forms to their local health department. Since deployment is staggered, at any point in time the non-intervention sites can act as natural controls for the intervention sites without the selection bias that is generally present in non-randomized experiments. Therefore, the study protocol is theoretically equivalent in its ability to generate causal evidence to a traditional randomized controlled experiment.

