### Data analysis (quantitative)

Quantitative analysis will provide measurable evidence of the impacts of the intervention and enable us to establish likely cause and effect. Longitudinal effects of the interventions will be evaluated in aggregate and across covariates on reporting rates, reporting timeliness and treatment timeliness using an interrupted time-series design to test for the intervention effect and the time trend post-intervention. This approach has been used in other decision support and time-series evaluations
[22] and has been recommended for multiple baseline time-series designs that involve two or more sites that are repeatedly assessed while an intervention is introduced into one site at a time
[23]. Since the effects of the interventions may vary across clinics, stratified regression analyses will also be performed. Following comparative assessment of reporting completeness, accuracy and communication burden, these data will be added to the regression model. Assessment of data completeness, timeliness, and accuracy will involve pre-post comparison of data quality metrics
[15].

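### Staggered deployment alone does not support the claims of freedom from selection bias and causal equivalence to a randomised experiment

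*Protocol article*

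**What the plan says.** The Intervention section of the protocol article sets out the rollout: "Two technical interventions will be deployed over a staggered schedule at participating clinics", namely the standard and the enhanced pre-populated forms. It then reasons in two steps.

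- First: "Since deployment is staggered, at any point in time the non-intervention sites can act as natural controls for the intervention sites". These controls are said to be "without the selection bias that is generally present in non-randomized experiments".
- Second, presented as the consequence of the first: "the study protocol is theoretically equivalent in its ability to generate causal evidence to a traditional randomized controlled experiment".

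Staggering is the only premise offered for either step. No section describes random allocation of clinics, or of the order in which they receive the forms.

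Three other places bear on the point.

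- The hypothesis at the end of the Background is comparative: it predicts better reporting than in clinics without the intervention.
- Data analysis (quantitative) plans to evaluate reporting rates, reporting timeliness and treatment timeliness "using an interrupted time-series design to test for the intervention effect and the time trend post-intervention". It places the study among multiple-baseline designs and claims causation only as likely.
- Limitations and biases concedes, for this same time-series design, that "confounding may occur due to covariates that may change over time".

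**The concern.** The value of a concurrent control depends on why a clinic is a control at that moment. If the order of entry depends on readiness, enthusiasm, information technology capacity or case mix, then the clinics that have the form and those still waiting can differ in level and trend, and in how they respond to outside changes. A staggered schedule does not prevent this. A random order would, in expectation.

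At stake is how strongly the results may be reported. The hypothesis is a comparison with clinics lacking the intervention, so the quality of those controls is central to it. Left as they stand, the two statements would allow a report to give interrupted time-series and pre-post findings the standing of a randomised comparison, although the same article calls them open to confounding.

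**Working it through.** The plan gives no figure for this claim, so there is nothing to reproduce numerically. The check is a short piece of algebra followed by a comparison of the sections.

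**What each design element removes.** Let E be clinics that receive a form earlier and L those that receive it later. Write the mean outcome of group g in calendar month t as

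Y_g(t) = a_g + b_g·t + c(t) + d_g(t) + δ·X_g(t)

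Here a_g is the group's level and b_g its underlying slope. The term c(t) is any change common to all clinics, and d_g(t) is any change over time specific to the group. X_g(t) is 1 once the form is in use and 0 before, and δ is the effect. While E has the form and L does not,

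Y_E(t) − Y_L(t) = δ + (a_E − a_L) + (b_E − b_L)·t + [d_E(t) − d_L(t)]

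1. The common term c(t) has cancelled. This is what staggering provides, and it is worth having.
2. The level and slope differences remain. They can be estimated from the pre-deployment series and removed if the model carries a level and slope for each group. That is the work of the baseline series and the model, not of staggering.
3. The group-specific changes d_E(t) − d_L(t) remain after both steps, except for what measured covariates explain.
4. If the order of entry is random, all three differences have expectation zero. That is what gives a randomised design its causal standing.

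The claim of no selection bias needs the terms in points 2 and 3 to vanish because of staggering. Staggering removes none of them.

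**The article's sections side by side.**

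| Section | What it supports |
|---|---|
| Intervention | No selection bias; causal evidence on a par with a randomised experiment; sole premise is staggering |
| Data analysis (quantitative) | Interrupted time series of multiple-baseline type; causation only likely |
| Limitations and biases | Confounding by covariates that change over time is possible |

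The second row is weaker than the first. The third row concedes the term in point 3: where covariates change differently in earlier and later clinics, d_E(t) − d_L(t) is not zero, and staggering gives no protection. The three sections cannot all stand as written.

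**The case against.** **The order may be random.** The article is a condensed document and is silent on how the order is set. A reader might infer that the order is known to be non-random; the text does not support that. The exact statement is that no randomisation is described. The point survives because the fault is an inference the article itself draws, from staggering alone.

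**The sentence is hedged and the limitations are disclosed.** The claim is qualified as theoretical, the primary research questions concern barriers and facilitators, and no model or decision rule is shown to depend on the sentence. This limits the consequences but does not rescue the claim: without a random order the equivalence fails in theory too, and disclosure elsewhere leaves the article inconsistent.

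**Stronger readings that the document does not support.**

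- A reader might take the admission that "some clinical sites may be more open to recruitment and enrollment in the study and thus introduce a bias in our sample" as a direct contradiction. It concerns entry to the study, and so mainly generalisability. A randomised trial in volunteer clinics would share it.
- The rotation of providers between sites would also trouble a cluster-randomised trial, so by itself it does not refute the equivalence.
- A reader might infer that no unexposed control exists once the last clinic has the standard form. That holds only if every comparison clinic eventually receives it, which the article does not say.
- A reader might multiply an assumed difference in monthly trend by the months of follow-up to obtain a spurious effect. The slopes would be invented, and the calculation is a raw early-versus-late comparison. The planned interrupted time series with a 12-month baseline would project a linear pre-existing trend rather than count it as effect.

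**Conclusion.** The point holds in this form: the article derives freedom from selection bias and equivalence to a randomised experiment from staggering alone, and neither follows. Both statements go beyond what its analysis section claims and conflict with the time-varying confounding it admits.

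The document does not allow the size of any bias to be bounded, and no figure is offered. The consequence is for the strength of inference: as described, the design supports a causal reading only on the assumption that, without the forms, earlier and later clinics would have followed comparable trends. The verdict rests on the article describing the design fully in this respect. If the order is in fact random, the claim has a better basis than the one given, but the stated reasoning would still need correcting.

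**What to change.** 1. Delete or qualify both statements in the Intervention section so that they agree with Data analysis (quantitative) and Limitations and biases. Possible wording: *Staggered deployment provides concurrent comparison clinics and helps to separate intervention effects from time trends common to all clinics. Causal interpretation assumes comparable underlying trends in earlier and later clinics.*
2. Describe the design as a staggered multiple-baseline interrupted time series, and state how the order of entry is set. If it is random, say so, describe the method and rest the claim on that.
3. Examine the trends of earlier and later clinics over the same calendar months of the 12-month retrospective baseline. Report the estimated difference in slope with its confidence interval. The article itself notes that one baseline year limits the handling of seasonality, so failure to detect a difference would not establish that the trends are equal.
4. If all participating clinics eventually receive the standard form, limit comparisons with unexposed controls to calendar time before the last one crosses.

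Items 1 and 2 cost nothing beyond rewording. Item 3 uses data already to be collected and needs only modest analysis time. Item 4 restricts the comparison period and needs no new data. Randomising the order, if deployment has not begun, would strengthen the design at the cost of some scheduling freedom. It is optional and not needed to cure the error.
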